## Abstract

Inflammation is an important pathophysiological process after an acute stroke (AS). Pro- and anti-inflammatory molecules (cytokines and interleukins) are the key players during this mechanism. Emerging evidence indicate that these molecules can serve as biomarkers of stroke progression and outcome and as novel therapeutics agents. The aim of this study is to explore the temporal changes in these molecules and validate them as biomarker of AS progression and neurological outcome.

The “Cytokine Registry In Stroke Patients (CRISP)” is a prospective cohort study of 600 AS patients presenting to the tertiary hospital with-in 24 h of the onset of symptoms. Plasma cytokines and interleukins will be collected at admission and 24 h after and will be measured using enzyme-linked immunosorbent assay (ELISA) to evaluate the difference in their variation among different gender, race and ethnicity and their association with various neurological outcomes. The primary exposures are biological sex (male, female) and race/ethnicity. Confounding variables include age, vascular risk factors, infarct size, stroke onset to presentation time, and identified stroke etiologies. Matched controls will be used for the comparison and evaluation of the difference among gender and race/ethnicities.

CRISP is a prospective observational study that investigates the role and relationship of molecular biomarkers identifying specific and relevant targets pertinent for monitoring the progression and outcome in AS patients.

Trial Registration: The study is registered on ClinicalTrial.gov: https://clinicaltrials.gov/ (NCT03297827).

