## Trial objective

2

The primary objective of the *“*Cytokine Registry In Stroke Patients (CRISP)” is to evaluate

1.the plasma concentration and time course of these pro- and anti-inflammatory cytokines and interleukins2.identification and establishment of a blood base bio-marker that can corroborate with the neurological outcome in these AS patients.

Our primary hypothesis is that temporal change in any one or more cytokine or interleukin levels during this early critical phase could be an important predictor of stroke severity. Moreover, separate sub-studies will explore and compare plasma cytokine levels based on gender, race, and ethnicity.

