### Study design

3.1

This is a prospective patient cohort registry (NCT03297827). Six hundred patients with the diagnosis of AS (IS and HS) will be recruited over the period of 3 years (2018–2021). The overview of the study design is presented in Figure 1. Plasma samples will be collected on admission and after 24 h. Plasma ILs (1, 4, 6, 10, 17, 23, 33, 36, and 37), platelet-derived growth factor (PDGF), vascular endothelial growth factor (VEGFM), tumor necrosis factor (TNF-a), ANNULIN, matrix metallopeptidase (MMP) 9 and 12, nuclear factor kappa-light-chain-enhancer of activated B cells **(**NFk-B), myeloperoxidase (MPO), glia-maturation factor (GMF), SI00 calcium-binding protein B (S100B), and GM6001 will be measured using enzyme-linked immunosorbent assay (ELISA).

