### Recruitment

3.5

This study will be performed at the tertiary care hospital. It will be conducted in accordance with the principles of Good Clinical Practice (GCP). The study protocol was approved by the Institutional Review Board (IRB). Study participants will be recruited through the department of Neurology after the written informed consent. Informed consent can be very challenging in AS patients. Patients may suffer from language deficit and/or other cognitive impairment that can hamper the informed consent procedure. The primary stroke team and/or the physician provider will assess the mental competence of the potential study participant to determine whether they are capable of giving informed consent. Hence, if the patient is ineligible the study will include the legal authorized representative (LAR) as part of the informed consent process. A study team member will obtain both verbal and written consent and will explain the study protocol to the potential participants. All the patients with the diagnosis of AS will be approached for the consent procedure. In addition, a flyer detailing an overview of the study protocol, as well as a copy of the formal consent form, will be given to potential trial participants. After obtaining the informed consent, the study team member will assign a unique study identification number (SIN) and enter the information in the REDCap database. After informed consent, a pre-randomization assessment for every recruiting patient will be done, evaluating their medical records for any autoimmune and/or inflammatory disorders.

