### Data analysis and sample size

3.6

The study team along with the core statistical division will evaluate all the study trial outcomes. One Way Analysis of Covariance (ANCOVA) will be employed, followed by post hoc tests while adjusting for multiple comparisons using the Sidak adjustment. As a secondary analysis, we will also look at the correlation network of these cytokines after stratification by sex and race/ethnicity. According to the ANCOVA model, based on 80% power and 5% significance level, the minimum sample size is 420 AS participants. The primary exposures are biological sex (male, female) and race/ethicity (American Indian/Alaskan Native, Asian/Pacific Islander, African American, Whites, and Hispanics). Confounding variables adjusted in the model include age, vascular risk factors, infarct size, and identified stroke etiologies. Matched controls will be used for the comparison and evaluation of the difference among age, gender, and race/ethnicities.

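### The aim to validate and establish a biomarker claims more than one single-centre cohort, with no marker fixed in advance, can support

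*Protocol article*

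**What the plan says.** The Abstract gives the aim as to "explore the temporal changes in these molecules and validate them as biomarker of AS progression and neurological outcome". Section 2 (Trial objective) makes "identification and establishment of a blood base bio-marker that can corroborate with the neurological outcome" part of the primary objective. The main hypothesis there reads: "temporal change in any one or more cytokine or interleukin levels during this early critical phase could be an important predictor of stroke severity".

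The design is one cohort. Section 3.1 states "Six hundred patients with the diagnosis of AS (IS and HS) will be recruited over the period of 3 years (2018–2021", and section 3.5 states "This study will be performed at the tertiary care hospital". Section 3.1 also says "Plasma samples will be collected on admission and after 24 h" and lists the analytes, starting with "Plasma ILs (1, 4, 6, 10, 17, 23, 33, 36, and 37" and continuing with eleven further molecules.

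Section 3.6 describes the analysis: "One Way Analysis of Covariance (ANCOVA) will be employed, followed by post hoc tests". The same sentence goes on to apply a Sidak adjustment to those post hoc tests. The primary exposures are sex and race/ethnicity, and a correlation network is secondary. Matched controls are for comparisons across age, gender and race/ethnicity.

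**The concern.** Exploring and validating are different tasks, as are identifying and establishing, and the article assigns both to the same study. Validation means that a marker, with its direction and preferably its threshold, was fixed before the data that test it were seen. Here nothing is fixed: the hypothesis is met by whichever analyte turns out to change with severity. The only other group described, the matched controls, cannot confirm a predictor of outcome after stroke.

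What is at stake is the conclusion. A report that follows the stated aim could call a marker validated when it has only been selected. If its discrimination were estimated in the patients used to select it, readers would also get a figure that is too high.

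**Working it through.** **1. The plan's own figure.** Section 3.6 gives a minimum of 420 participants from the ANCOVA model at 80% power and 5% significance. It cannot be reproduced, because the article gives no effect size. Working backwards with an F test and 5 covariate degrees of freedom (assumed), 420 corresponds to Cohen's f = 0.137 for sex (1 df), 0.170 for race/ethnicity (4 df) or 0.195 for ten sex-by-race cells (9 df). On any of these readings it concerns group differences in analyte level, so it neither supports nor undermines a claim about predicting outcome.

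**2. Number of candidates (section 3.1).**
- Analytes: 9 interleukins + 11 others (PDGF, VEGF, TNF-α, annulin, MMP-9, MMP-12, NF-κB, MPO, GMF, S100B, GM6001) = 20.
- Readings: 20 × 2 times = 40.
- Features, if the change is counted as well: 20 × 3 = 60. The change is fully determined by the two levels, so this is an upper count.

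**3. Optimism for one selected marker.** Assumptions not in the article: a binary poor outcome in 20% or 40% of patients, AUC as the measure, correlation 0.3 between markers, and the best apparent AUC chosen and reported in the same patients. Mean apparent AUC over 300 simulated cohorts of 600:

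| Candidates | True AUC | Apparent, 40% poor outcome | Apparent, 20% poor outcome |
|---|---|---|---|
| 20 | 0.50 | 0.550 | 0.560 |
| 60 | 0.50 | 0.558 | 0.573 |
| 20 | 0.584 | 0.623 | 0.632 |
| 60 | 0.584 | 0.629 | 0.639 |

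The true value 0.584 is Φ(0.3/√2), a standardised difference of 0.3 in every marker. A separate simulation of 20 analytes with two levels and a change each (40% poor outcome, correlation 0.5 between the two samples) gave 0.562 and 0.558 under the null, for between-analyte correlation 0 and 0.3.

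Plausibility check: the null standard error of an AUC is √[(n+1)/(12·n₁·n₀)].
- 40% poor outcome: √[601/(12 × 240 × 360)] = 0.0241.
- 20% poor outcome: √[601/(12 × 120 × 480)] = 0.0295.

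The best of 20 therefore lies 0.050/0.0241 = 2.1 or 0.060/0.0295 = 2.0 standard errors above 0.50, which is about what picking the largest of 20 correlated values should give.

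**4. Optimism for a panel.** The article proposes no such model; this only shows the direction. With 30% poor outcome, n = 600 and a linear score on all markers, apparent AUC against AUC in new patients is:
- 20 markers: 0.61 against 0.50 with no true marker, and 0.69 against 0.63 with three true markers (standardised difference 0.3).
- 40 features: 0.66 against 0.50, and 0.72 against 0.62.

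**5. What Sidak would do.** It is stated for the post hoc tests that follow the ANCOVA. If it were carried across 20 analytes, the per-test level would be 1 − 0.95^(1/20) = 0.00256 and the family-wise error would be held at 5% for independent tests. That limits how often a null marker is declared. It does not alter the estimated AUC of the marker that is declared, so the optimism in steps 3 and 4 remains.

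**The case against.** The strongest objection is that much of this could be settled in a document not shown. A journal article condenses the full protocol, and bootstrap or cross-validation normally sits in the analysis plan. A reader might infer that reported performance will be inflated, or that the plan is at fault for having no internal validation. The article supports neither: it states no selection rule, no marker-to-outcome model and no performance measure, and its silence on internal validation is not an error. This part of the objection stands, and the bias is conditional.

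A reader might also take the ANCOVA as evidence of validating on the selection data. It is not. Its exposures are sex and race/ethnicity, so it does not address marker performance either way. Nor is 1 − 0.95^20 = 64% a fair measure of the problem. It assumes unadjusted independent tests, ignores the stated Sidak adjustment, and describes false positives rather than optimism.

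The word 'validate' could also mean re-testing markers reported elsewhere. The Introduction cites TNF-α, IL-1, IL-6, IL-10 and S100B as already studied. For markers named in advance and tested without selection, this cohort would be a fair replication. That reading is open in principle, but the article names none of them as the marker to be confirmed.

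Finally, the text elsewhere uses cautious language for an observational registry, and the single-marker optimism at n = 600 is modest. Both are true. Neither removes the mismatch between the stated aim and the design, because no analysis plan can supply the independent cohort that the described design lacks.

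**Conclusion.** The point holds as a mismatch between claim and design. The aim and the primary objective promise validation and establishment, while the described study can only identify candidates, at best with internally validated performance. This rests on the article's own statements and needs no simulation.

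The numerical part is conditional on selecting and reporting in the same patients without correction. At n = 600, under the assumptions listed, the best single null marker would show an apparent AUC of about 0.55 to 0.57. With true AUC 0.584 the excess is 0.04 to 0.06 (0.623 − 0.584 to 0.639 − 0.584). A many-marker score would show more: an excess of about 0.06 (0.690 − 0.633) to 0.16 (0.660 − 0.501) in the cases tried. These sizes depend on outcome prevalence, marker correlations and a choice of model that the article does not give.

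**What to change.** 1. In the Abstract and section 2, restate the biomarker aim as identifying candidate biomarkers of progression and neurological outcome.
2. State that performance of any marker or panel selected in this cohort is reported only after internal validation that repeats the whole selection step, across all analytes and all readings considered. Bootstrap optimism correction is one example. If the analysis plan already does this, a cross-reference is enough.
3. Keep 'validate' and 'establish' for confirmation in an independent cohort, or for markers named before the data are seen, on the strength of prior literature, and tested here without selection.

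The cost is wording and some computation, with no further patients, samples or assays. The downside is a more modest claim and lower reported performance.

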## Introduction

1

Stroke is a neurologic deficit occurring due to interruption of cerebral blood flow or from bleeding by a ruptured blood vessel in the brain.^[1,2]^ According to World Health Organization (WHO), it is the second leading cause of deaths worldwide.^[3]^ In the United States (US), it is the fifth leading cause of mortality killing around 140,000 Americans each year and the leading cause of morbidity and complex disability.^[4,5]^

During acute stroke (AS), the deprivation of oxygen, glucose, and other nutrients to the brain causes dysfunction of the neurovascular unit. Additionally, the breakdown of the blood–brain barrier, and induction of the inflammatory cascade results in subsequent brain damage.^[6,7]^ This is characterized by an increase in multiple pro-inflammatory and decrease in anti-inflammatory cytokines, which also correlates with progression of stroke injury.^[6,8]^ Various pro-inflammatory cytokines are observed in experimental models and in stroke patients that may correlate with infarct size and stroke outcomes.^[9–14]^ Cytokines and interleukins including TNF-α, interleukin (IL)-1, IL-6, and IL-10, have been studied as therapeutic and prognostic markers in AS.^[10,12,15,16]^ IL-10 is an anti-inflammatory molecule, observed to be associated with negative feedback, whereas IL-6 and TNF-α are reported to be increase in both ischemic and hemorrhagic stroke patients.^[11,16,17]^ Moreover, glial cell markers such as S100B and various other cytokines have also been reported to be associated with infarct size, neurological outcome, and prognosis among these patients.^[10,17–21]^

The inflammatory mechanism and the interaction between the pro- and anti-inflammatory cytokines in AS patients is still ambiguous. Although, studies have indicated changes in systemic cytokine profile in response to experimental stroke, few studies have assessed peripheral cytokine levels in human stroke patients and their association with the neurological outcome.^[10]^ As such, for the use of cytokines as potential biomarkers and prognosis of stroke, it is important to design clinical stroke studies on peripheral cytokine expression that focuses on the temporal profile, comorbidities, and demography.

## Trial objective

2

The primary objective of the *“*Cytokine Registry In Stroke Patients (CRISP)” is to evaluate

1.the plasma concentration and time course of these pro- and anti-inflammatory cytokines and interleukins2.identification and establishment of a blood base bio-marker that can corroborate with the neurological outcome in these AS patients.

Our primary hypothesis is that temporal change in any one or more cytokine or interleukin levels during this early critical phase could be an important predictor of stroke severity. Moreover, separate sub-studies will explore and compare plasma cytokine levels based on gender, race, and ethnicity.

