### Data Collection

3.3

Patients who will meet all inclusion criteria/exclusion criteria will be consented. Two sets of plasma samples will be obtained from individual participants; one upon admission to the hospital, and the second sample 24 h apart from the first one. Both sets of blood samples (3–5 mL) will be collected from peripheral veins according to the routine puncture method as standard of care. After centrifugation, the resulting plasma supernatants will be stored at −80°C. The samples will be transported and handled according to the federal guidelines. Additional hospital data will be collected by chart review. This includes last known well or the time of onset of symptoms (according to patient or bystander), the presence of any neurological deficit or hemiparesis (if applicable), demographics, vital functions, neurological examination (NIHSS), imaging include non-contrast CT scan, CT angiography (CTA), digital subtraction angiography (DSA), and/or CT perfusion, clinical data including medical history, comorbidities, medication use, laboratory results, and physical examination will be collected using the chart review. Information regarding the corresponding treatment including door to needle time and door to groin time will be also collected. Other parameters like length of hospital stay, discharge location, and modifies Rankin Scale (mRS) at 3 months will be collected as part of the protocol. All paper consents will be secured in the locked cabinet in the principal investigator (PI) office. The PI's research team will be responsible for consenting, collecting samples, storage in secure refrigerator, running the assays and entering the inferences and other clinical details into a secure REDCap database.^[22]^ REDCap (Research Electronic Data Capture) is a secure, web-based application designed to support data capture for research studies, providing

1.an intuitive interface for validated data entry;2.audit trails for tracking data manipulation and export procedures;3.automated export procedures for seamless data downloads to common statistical packages; and4.procedures for importing data from external sources.

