### Study outcomes

3.4

The primary objective of this study is to measure the levels of the reported cytokines and other analytes that have a continuous measure, from the plasma of AS patients using standardized ELISA kits. The primary exposures are biological sex (male, female) and race/ethnicity (American Indian/Alaskan Native, Asian/Pacific Islander, African American, Whites, and Hispanics). Confounding variables to adjust for are age, vascular risk factors, medications (anti-inflammatory), infarct size, stroke onset to presentation time, and identified stroke etiologies (based on TOAST criteria).

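### The article disagrees with itself on its primary question: Section 2 makes cytokine change as a predictor of severity primary, but the stated analysis and sample size serve the sex and race/ethnicity comparison

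*Protocol article*

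**What the plan says.** **Section 2 (Trial objective).** The primary objective has two parts: the concentration and time course of the analytes, and a "blood base bio-marker that can corroborate with the neurological outcome in these AS patients". The hypothesis labelled primary reads: "temporal change in any one or more cytokine or interleukin levels during this early critical phase could be an important predictor of stroke severity". The demographic comparisons are placed outside this: "separate sub-studies will explore and compare plasma cytokine levels based on gender, race, and ethnicity".

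**Abstract.** The measurements are meant "to evaluate the difference in their variation among different gender, race and ethnicity and their association with various neurological outcomes". The Abstract also names sex and race/ethnicity as the primary exposures.

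**Section 3.4 (Study outcomes).** The primary objective is restated as being to "measure the levels of the reported cytokines and other analytes that have a continuous measure", and "The primary exposures are biological sex (male, female) and race/ethnicity".

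**Section 3.6 (Data analysis and sample size).** "One Way Analysis of Covariance (ANCOVA) will be employed", followed by Sidak-adjusted post hoc tests. The minimum of 420 patients (80% power, 5% significance) is attributed to the ANCOVA model. Sex and race/ethnicity are again the primary exposures. The other stated analyses are a correlation network of the cytokines, stratified by sex and race/ethnicity, and a comparison with matched controls.

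**Section 3.3 (Data Collection).** Two plasma samples 24 h apart, the NIHSS, length of stay and discharge location are recorded, and the "modifies Rankin Scale (mRS) at 3 months will be collected as part of the protocol".

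**The concern.** The hypothesis and the analysis point in different directions. In Section 2 the analyte is the explanatory variable and the patient's severity or outcome is what it should explain. In Sections 3.4 and 3.6 sex and race/ethnicity are the explanatory variables and the analyte appears to be the response. The comparison that Section 2 sets apart as sub-studies is the one that receives the named method, the multiplicity adjustment and the sample size.

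Two things are at stake. An analyst who follows Section 3.6 to the letter will produce sex and race/ethnicity contrasts and no estimate for the primary hypothesis. A reader of the eventual report may also take the 80% power statement to apply to the outcome question, for which the article gives no calculation. Because the hypothesis would be met by any one or more of the analytes, an outcome analysis chosen after the data are seen would be hard to defend as confirmatory.

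**Working it through.** **1. What each stated analysis can answer**

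| Analysis in Section 3.6 | 24 h change as predictor? | Severity or outcome as dependent variable? |
|---|---|---|
| One-way ANCOVA with Sidak post hoc tests | No: the exposures are sex and race/ethnicity | No: analyte level, as inferred from Section 3.4 |
| Stratified correlation network | No: relates cytokines to each other | No |
| Matched-control comparison | No: compares groups | No |

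Analyses that address the primary hypothesis: 0 of 3. Section 3.6 does not name the ANCOVA's dependent variable. If it were the 24 h change rather than a level, change would still be the response and not the predictor. The covariates listed there (age, vascular risk factors, infarct size, etiology) include no NIHSS, mRS or change score.

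**2. What the 420 covers**

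The article gives no effect size, covariate R² or group shares, so 420 can be neither reproduced nor refuted. One can solve for the effect that it implies. With the noncentral F distribution, λ = f²·N and df₂ = N − groups − covariates, at 5% significance and 80% power with N = 420 and 4 covariates:

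- sex (df₁ = 1): f = 0.137, which for equal groups is d = 2 × 0.137 ≈ 0.27
- five race/ethnicity groups (df₁ = 4): f = 0.170
- ten sex-by-race cells (df₁ = 9): f = 0.195

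With 0 or 6 covariates these values are the same to three decimals for sex and the ten cells, and 0.170 after rounding for race/ethnicity. On each reading the figure describes a difference between demographic groups. None describes an association between change and outcome.

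**3. What the same patients could detect for the Section 2 hypothesis (illustration)**

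Assumptions, none of them from the article: a Fisher-z test of the partial correlation r between 24 h change and a severity or outcome score, 6 covariates, two-sided 5%, 80% power. An ordinal outcome would need its own calculation.

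Formula: r = tanh[(z₁₋α/₂ + z₀.₈) / √(N − 3 − 6)].

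Section 3.1 lists 9 interleukins and 11 other analytes, 20 in all. The Sidak per-test level is 1 − 0.95^(1/20) = 0.00256.

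| N | One analyte, α = 0.05 | 20 analytes, α = 0.00256 |
|---|---|---|
| 420 | 0.137 | 0.188 |
| 600 | 0.115 | 0.157 |

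Example: for N = 600 and 20 analytes, (3.016 + 0.842)/√591 = 0.1587, and tanh gives 0.157.

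Conversely, the N needed with Sidak over 20 is 1488 for r = 0.10, 661 for r = 0.15, 372 for r = 0.20 and 165 for r = 0.30. Whether 600 is enough therefore depends on an r that the article does not state.

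**The case against.** The strongest reply is that this is a journal article and that the outcome model belongs in a fuller protocol or analysis plan. The Abstract does name association with neurological outcomes as a purpose, and Section 3.6 says in general terms that all outcomes will be evaluated. The absence of a regression specification would therefore not be a finding by itself. This part stands. What remains is that the article does fix a method, exposures, covariates, a multiplicity adjustment and a sample size, and fixes them for a question that Section 2 calls a sub-study. An analysis plan that followed Section 3.6 would leave the primary hypothesis without a test; one that followed Section 2 would contradict Sections 3.4 and 3.6.

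It can also be said that Section 2 may be the outlier, because the Abstract agrees with Sections 3.4 and 3.6 on the primary exposures, and because measuring analyte levels partly matches the first part of the Section 2 objective. That is fair. The text does not show which version was intended, so it supports reconciliation and not a ruling for Section 2.

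A reader might infer more than the documents support:

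- *That the sex and race/ethnicity ANCOVA is the only planned analysis, or that the hypothesis will never be tested.* Section 3.6 also states the network and the control comparison, and the full protocol is not shown. The supportable statement is that no analysis stated in this article tests the hypothesis.
- *That change over 24 h cannot logically predict severity.* This assumes severity at presentation. Section 2 does not say so, and Section 3.3 gives the NIHSS no assessment time.
- *That a marker will be picked from a large grid of marker-outcome pairs.* The article describes no such search, and any count depends on which collected items are treated as outcomes.

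**Conclusion.** The point holds as an internal contradiction over what is primary. Section 2 on one side, and the Abstract with Sections 3.4 and 3.6 on the other, cannot both describe the primary question. None of the three analyses stated in Section 3.6 estimates the effect named in the primary hypothesis, and the 80% power at 420 patients belongs to the ANCOVA alone.

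This rests on one inference, that the ANCOVA's dependent variable is the analyte measurement; Section 3.4 supports it, but Section 3.6 does not say so. It does not rest on the correlation figures, which only show the order of effect that the planned 600 could detect under assumed inputs. The design is observational and the hypothesis is worded cautiously, but it is still labelled primary, so the conflict should be settled before any analysis.

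**What to change.** Reconcile Sections 2, 3.4 and 3.6, and bring the Abstract into line, by one of two routes.

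**If Section 2 governs:**
- Name a primary analysis that regresses an outcome measured after the second sample on the 24 h change of each analyte. Ordinal regression of the 3-month mRS is one suitable option, not the only one.
- Adjust for the admission level of the analyte and for collected prognostic covariates, such as age, stroke type and onset-to-sample time. Include the NIHSS as a baseline covariate only if it is recorded at admission, and state that time.
- Specify multiplicity control across the 20 analytes.
- Label the sex and race/ethnicity ANCOVA secondary.
- State that the 80% power at 420 applies to the ANCOVA only, and give the detectable association for the outcome model at 600.

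**If sex and race/ethnicity are truly primary:** restate the objective and hypothesis in Section 2 accordingly, and label the outcome association exploratory.

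**Cost.** Mainly wording and one added calculation. The two samples, the NIHSS and the 3-month mRS are already in the data collection. Either the demographic comparison or the outcome hypothesis loses its primary label. Under the first route the existing power statement no longer supports the primary question, and the outcome model may prove underpowered at 600 if the true association is weak.
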